## Methods

### Study design

This study evaluates the effect of a self-management education program on several indicators of disease activity and associated psychosocial and physiological variables in patients diagnosed with RA and will take place in Bavaria, Germany, from March 2022 to December 2024. Enrolled patients (*n* = 440) will be randomly assigned (randomized) in equal numbers to either an intervention (*n* = 220) or control group (*n* = 220). The intervention group will participate in 15 2-h sessions over nine months in subgroups of 6–12 participants, aimed at enhancing individual health and life skills. The program will be led by psychotherapists who are specifically trained.

The training subgroups will not run simultaneously but will start independently whenever enough patients in a region have enrolled to form an intervention subgroup. To evaluate the effect of this intervention, various indicators of RA disease activity, immune and stress system activity, and psychological condition will be assessed through a set of standardized questionnaires and biochemical analyses of blood, urine, and saliva samples. Outcome variables will be measured at regular intervals before the intervention (baseline), during the 9-month intervention (five time points), and during the 9-month follow-up phase (three time points) at patients’ appointments with their respective rheumatologists. Further data on health-related costs will be acquired through the participating insurance companies (BKK-LV Bayern and AOK Bayern). The subsequent statistical analysis will then assess intra- and interindividual effects based on comparing time points and study groups. Furthermore, a total of ten patients (*n* = 5 from the intervention group, *n* = 5 from the control group) will be investigated thoroughly in integrative single-case studies [21] using biopsychosocial measurements collected at 12-h intervals to produce time-series data for approximately 1 month before and after the intervention. Patients allocated to the control group will receive an expense allowance of 260 Euros to cover the 26 h required for project-related activities during the nine time points of the study (equivalent to ten euros per hour). All patients will continue to receive standard treatment from their rheumatologists during the study. An overview of the study’s timeline can be seen in Fig. 1. No adverse events or harm is expected from the study.

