### Outcome measures

Measurements of the target variables and additional data will be collected at multiple time points throughout the study period by participating rheumatologists and psychotherapists (Fig. 1). The first measurement time will be a maximum of 2 weeks prior to the intervention as a baseline (*t*_0_). Then, five more measurements will be taken every 6 weeks during the 9 months of intervention (*t*_1_: 1.5 months after intervention start, *t*_2_: after 3 months, *t*_3_: after 4.5 months, *t*_4_: after 6 months, *t*_5_: after 9 months) and three more measurements will be taken every 3 months during the follow-up phase (*t*_6_: after 12 months, *t*_7_: after 15 months, *t*_8_: after 18 months). The time points will have a temporal range of ± 2 weeks for each proband, depending on each participant’s appointment at the rheumatologist’s office.

The psychological condition of each participant will be determined with a set of questionnaires. The State-Trait Anger Expression Inventory-2 (STAXI-2) is a questionnaire that measures various aspects of anger as an emotional state (state anger) and the disposition to experience angry feelings as a personality trait (trait anger) [27]. The Toronto Alexithymia Scale (TAS-26) assesses difficulties in identifying and describing feelings or emotions [28]. The 12-item Short Form Survey (SF-12) captures the general physical and mental health status and its implications for an individual’s everyday life [29].

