Physiological measurements will be assessed in blood and saliva samples, which the rheumatologists will collect at each appointment from the patients. Several cytokines and associated parameters, namely, tumour necrosis factor α (TNF-α), interleukin-1β (IL-1β), interleukin-2 (IL-2), interleukin-2 receptor (IL-2R), interleukin-6 (IL-6), interleukin-10 (IL-10), interleukin-12 (IL-12), interleukin-13 (IL-13), C-reactive protein (CRP), and erythrocyte sedimentation rate (ESR), will be analysed in plasma samples to assess immune system activity. Furthermore, cortisol levels will be measured in saliva samples. Cytokine and cortisol concentrations will be assessed at all time points. Additionally, at *t*_0_, anti-citrullinated protein antibody (ACPA) and IgG Fc autoantibody (rheumatic factor) levels will be measured. The rheumatologists are responsible for sampling and preprocessing all specimens and will determine ACPA, rheumatic factor, and CRP/ESR levels at *t*_0_, *t*_1_, *t*_3_, and *t*_5_–*t*_8_ within the frame of standard patient care. An external professional laboratory will be engaged to perform all other biochemical analyses in this study. For shipment from the rheumatologists to the laboratory, blood samples will be centrifuged (3000 rpm for 10 min) in serum gel tubes and subsequently stored at − 20 °C, and saliva samples will be collected using a cotton swab and shipped at room temperature.

RA disease activity will be measured using the Disease Activity Score 28 (DAS 28), the Simplified Disease Activity Index (SDAI), and the Clinical Disease Activity Index (CDAI) [34]. These composite scores are standard in clinical practice and based on questions about rheumatic pain, swelling, and tenderness of joints evaluated by the patient and the attending physician, combined with levels of CRP/ESR. Additionally, the Hannover Functional Ability Questionnaire (FFbH) will be conducted to assess functional capacity and impairment during rheumatic patients’ daily activities [35]; the patients rate their overall pain on a 10 cm visual analogue scale (VAS). The DAS 28, SDAI, CDAI, and pain VAS will be assessed at all measurement time points by the rheumatologists; the FFbH will be administered at every second time point (*t*_0_, *t*_2_, *t*_4_, *t*_6_, and *t*_8_).

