After enrolment, the patients will be randomly allocated to the intervention or control group in a 1:1 ratio, alternately dependent on the time of registration, using a prefabricated list of pseudonymous six-digit proband IDs created using the *random*-package in Python [41]. These IDs will be used to combine data from different sources for evaluation purposes pseudonymously. The UR will be responsible for evaluating study data and monitoring the project progress, whereby data from different sources (RheMIT, archive service provider, laboratory, BKK-LV Bayern, AOK Bayern) will be combined and sorted according to the proband IDs. If missing data or unattended appointments are found, the UR will contact respective responsibilities to evaluate further procedures.

A designated proband guide will handle a large part of the communication and information flow towards patients, rheumatologists, and psychotherapists. The BKK-LV Bayern and AOK Bayern will inform the proband guide about each enrolled patient, who will then inform the patients about their group allocation and patients in the intervention group about possible intervention subgroups near them. When 6–12 participants are available for a subgroup, the proband guide will close admissions for that subgroup, set an intervention start date, and provide the participants' contact information and questionnaire copies (NEO-FFI, anamnesis and evaluation form) to the assigned psychotherapist. Each psychotherapist leading a subgroup will track the attendance of participants at each session and transmit lists to an archive service provider, who will forward these to the UR.

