Furthermore, the proband guide will inform the rheumatologists of the patients in each subgroup so that they can arrange appointments at the measurement time points (*t*_0_–*t*_8_). For secure exports of datasets to the study's evaluators, some of the measurements that are assessed in these appointments (CRP/ESR, SDAI, CDAI, DAS 28, VAS, PHQ9, FFbH, PSQI, BMI, medication, comorbidities, rheumatic factor levels, ACPA levels) will be documented by the rheumatologists using standardized forms in particular software (RheMIT | BDRh Service GmbH [bdrh-service.de]). The UR will receive the pseudonymized (proband ID) data for all patients, while the MUI will receive only data for the integrative single-case study patients. Other questionnaires, which will also be administered at the appointments and cannot be documented in RheMIT (STAXI-2, TAS-26, SF-12, heiQ, PETRA-Questionnaire), and the questionnaires, which will be completed during the intervention’s group sessions with the psychotherapist, will be mailed by the rheumatologists and psychotherapists to an archive service provider, who will digitalize the data and forward it to the UR. Data from the integrative single-case study participants will then be sent to the MUI by the UR. The data on healthcare-related costs will be pseudonymized and sent directly to the UR by BKK-LV Bayern and AOK Bayern.

For physiological measurements performed by the external professional laboratory, the rheumatologists will send preprocessed samples (blood and saliva) to the laboratory, where the mentioned biochemical analyses will be performed, and the pseudonymized results will be transmitted to the UR. In the integrative single-case studies, laboratory equipment necessary for urine sampling and storage and all questionnaires will be provided to the patients before the data sampling period starts and will be picked up afterwards by the MUI. The MUI will perform subsequent biochemical analyses of urine samples.

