All patient data transfers will be performed securely, either by mail or encrypted email. The data flow architecture and study procedures have been reviewed and approved by the Bavarian state commissioner for data protection. In this study, a data monitoring committee has not been established. To ensure that the data from the various sources are transferred securely to the UR (evaluating institution), a server will be rented from the company Pegasus GmbH. Pegasus GmbH will assume the role of security management and manage server hosting. Pegasus GmbH is ISO/IEC 27001 and ISO/IEC 27018 certified. The servers are in Germany. Before the exchange, all files to be transmitted will be encrypted. For this purpose, asynchronous encryption is used. Each partner, similar to the UR, creates a private and a public key, and they exchange these keys among one another. The files are signed using the partner’s private key so that the recipient can verify the sender’s source, and the files are encrypted using the partner’s public key so that only the owner of the key counterpart can decrypt them. The study design is open-label with only outcome assessors being blinded, so unblinding will not occur.

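### The blinded-assessor statement cannot hold for DAS 28, SDAI and CDAI, because the rheumatologists who assess them are told who is in each intervention subgroup

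*Protocol article*

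**What the plan says.** Four parts of the protocol article bear on this point.

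- **Blinding.** Study procedures and data management ends with: "The study design is open-label with only outcome assessors being blinded, so unblinding will not occur". The term outcome assessor is not defined there or elsewhere.
- **Who assesses.** Outcome measures says: "The DAS 28, SDAI, CDAI, and pain VAS will be assessed at all measurement time points by the rheumatologists". The composite scores rest on "questions about rheumatic pain, swelling, and tenderness of joints evaluated by the patient and the attending physician", combined with CRP/ESR.
- **What the assessors are told.** Study procedures and data management says that "the proband guide will inform the rheumatologists of the patients in each subgroup so that they can arrange appointments" at t0 to t8.
- **What a subgroup is.** Under Study design, training subgroups "start independently whenever enough patients in a region have enrolled to form an intervention subgroup". The allocation text in Study procedures and data management has the proband guide inform "patients in the intervention group about possible intervention subgroups near them". Intervention gives their size as 6–12 participants, led by a psychotherapist.

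**The concern.** Joint swelling and tenderness call for judgement by the examining physician, and blinding the assessor is the usual protection for such ratings in an open-label trial. If the examiner knows the arm, belief in the programme can move the score without any change in the joints.

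The article reports that this protection is in place, while its own scheduling procedure removes it for the disease-activity scores. Anyone judging risk of bias from the published protocol would credit these scores with blinded assessment. The limitations in the Discussion do not correct that impression: they cover generalisability, self-selection of volunteers and the lack of an active control, but not unblinded assessment.

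**Working it through.** No formula applies. The check traces who produces each outcome and what that person is told.

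**Step 1: what the scheduling notice reveals.** Study design, Population, Intervention and the allocation text all use the word subgroup for intervention groups only. No sentence places a control patient in one. A rheumatologist told which patients belong to a subgroup therefore knows they are in the intervention arm and can infer that the other enrolled patients are controls.

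**Step 2: when it is revealed.** The notice serves to arrange t0 to t8. Since t0 is among those visits, the disclosure comes no later than the arrangement of the baseline visit.

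**Step 3: status by outcome.**

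- *DAS 28, SDAI, CDAI, physician-rated part:* the assessor is the rheumatologist, who is told subgroup membership. Not blind under the stated procedure.
- *The same scores, patient-rated part; pain VAS; questionnaires:* the patient gives the rating and is told the allocation. Not blind, but this is what open-label already says.
- *CRP/ESR:* determined by the rheumatologists within standard care. These are measured values rather than ratings.
- *Cytokines and salivary cortisol:* analysed by an external laboratory, which returns pseudonymised results. Blinding is possible but not stated.
- *Healthcare costs and use:* routine insurance data, which no study assessor rates.

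**Step 4: can another meaning of assessor save the statement for the disease-activity scores?** If it means the evaluating university, that institution receives session attendance lists, which only intervention patients can generate. If it means the laboratory, the statement may be true, but the laboratory does not rate joints. Neither reading makes the assessment of DAS 28, SDAI or CDAI blind.

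**Step 5: are there visits left to protect?** The last visit, t8, falls 18 months after the start of the intervention. Version 5.0 is dated 24 October 2023, and 18 months earlier is 24 April 2022. Anyone whose 18 months began after that date still had at least one visit due. Recruitment ran to 30 September 2023, so some visits very probably remained.

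**The case against.** **The term is undefined.** The blinding sentence closes a paragraph on data transfer and could refer to the laboratory. This stands as a limit: a reader might infer that the statement is false throughout, but the article supports only that it is untenable for the rheumatologist-assessed scores.

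**The scheduling sentence may be loosely worded.** It is the only description of how rheumatologists learn whom to schedule, yet controls follow the same visit plan. If subgroup means intervention patients only, no route is given for control visits, so perhaps controls were meant to be included. That is possible, but every other use of the word points the other way, and nothing says that the arm is withheld from the rheumatologist.

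**The closing clause may be over-read.** The words on unblinding may mean only that an open-label trial needs no unblinding procedure. This is a fair reading. The conflict lies in the claim of blinded assessors and does not depend on that clause.

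**Patients know their arm in any case.** This is correct and already disclosed by the open-label label. It is not a further error, and only the physician's contribution is at issue.

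**The tempting figure.** A reader might convert the planned f = 0.1 into d = 2 × 0.1 = 0.2 and say that a rating shift of 0.2 SD would equal the whole target effect. The article does not support this. Its f comes from mixed-model simulations, its central question is the group-by-time interaction, and the conversion is for a simple two-group comparison. No figure for rating bias is given. A constant shift present from t0 onward would also fall into the group main effect; only a between-arm shift that changes over time would imitate the interaction.

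**Conclusion.** The point holds for DAS 28, SDAI and CDAI. The article claims blinded assessors, and its own flow of information discloses the arm to the people who assess these scores. It rests on one assumption, that subgroup in the scheduling sentence has the meaning it has everywhere else in the article.

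The consequence is a risk of expectation bias in the physician-rated part of the scores, of a size that cannot be derived from the document. Two wider inferences are not supported. One is that laboratory values are the only outcomes not rated by someone who knows the arm: the insurance data are not rated by an assessor either. The other is that a disease-activity benefit should count only if a marker such as IL-6 agrees. That would be a new success criterion, and the article's Background lists IL-6 under anti-inflammatory activity, so even the direction of agreement is not settled.

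**What to change.** 1. Reconcile the blinding statement with the assessor and scheduling text. Withdraw the claim for rheumatologist-assessed scores. Name the assessors who are blinded and how allocation is kept from them. The external laboratory should be listed only if its blinding is confirmed, since pseudonymised results alone do not establish it.
2. For visits still to come, have the proband guide send one identical, arm-neutral notice per patient in both arms, giving appointment dates and no reference to a subgroup. Ask patients not to mention their group during joint assessment. Optionally, record the assessor's guess of the arm.
3. Report visits already held as not assessor-blind, and interpret the disease-activity results in that light.

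The second step cannot restore blinding where a rheumatologist already knows a patient's arm, so the first and third matter most. The cost is a changed form, at most one extra question, and a blinding statement that reads less favourably.

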### Statistical analyses

A central question in the statistical analyses represents the interaction of the intersubject factor group membership (intervention or control group) and the intrasubject factor time of measurement, i.e. the question of the target variables’ different trajectories in the intervention and control group. For longitudinal data analysis, generalized linear mixed models will be estimated, and due to their flexibility, they can model both normally distributed data and count data as dependent variables. In addition, missing values due to drop-outs are less of a problem for mixed longitudinal models compared to analyses of variance, providing a major advantage in analysing clinical programs. For all outcome variables, covariates will be included in the analyses as potential predictors (e.g. age, personality, gender, the severity of illness at baseline).

In the context of these generalized linear mixed models, quasi-Poisson regressions are the preferred method for modelling healthcare-related costs, which are associated with the predictors through log-link functions. Quasi-Poisson regression is preferred over classic Poisson regression for this project because it also allows modelling overdispersion in count data through an additional variance parameter. Immunoendocrine marker levels, questionnaire data and healthcare-related data with an approximated normal distribution, in turn, can be modelled linearly or estimated according to the divergent distribution with a fitted link function. Comparisons between the intervention and control groups will be directly integrated into the mixed regression models with a dichotomous indicator variable, whereby the influence of other covariates in the comparison can be accounted for. Statistical significance is indicated by a *p* value < 0.05. In addition, the Benjamini–Hochberg method will be applied as a correction procedure to avoid the inflation of type I errors in multiple analyses.

In the statistical analyses of the integrative single-case studies, time series variables will be tested on mutual dependency using autoregressive integrated moving average models (ARIMA), cross-correlational analyses and vector autoregressive models (VAR). First, it will be necessary to consider that each time series––psychosocial or biochemical––is governed by two main factors: an internal dynamic structure, giving rise to serial dependency, and serially uncorrelated disturbances. Because of such serial dependencies, an unadjusted cross-correlational analysis may lead to spurious correlations. Therefore, these dependencies will be separated from the disturbances by applying ARIMA filters to the time series. To determine whether one variable significantly precedes and thus predicts another, cross-correlations with the filtered residuals will be computed, both at lag zero (i.e. contemporaneous correlation) and higher lags (up to ± 14) with a significance level of *p* < 0.05.

All planned analyses will be performed with both the newest version of IBM SPSS Forecasting [42] and statistical software *R* [25] using the packages *lme4* (generalized linear mixed-effects models) [24], *tseries* (basic time-series analysis) [43], *forecast* (ARIMA models) [44], *vars* (VAR models) [45], and *ggplot2* (graphical processing) [46].

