## Abstract

Rheumatoid arthritis (RA) is a chronic autoimmune disease that primarily affects cartilage and bone. Psychological stress can both trigger disease exacerbation and result from disease activity. As standard pharmacological interventions alone have limited success in treating RA, a more comprehensive biopsychosocial approach to treatment has been recommended. In this prospective randomized controlled trial (RCT), a psychotherapeutically guided, group-based intervention program will be conducted with RA patients over a period of 9 months. This program combines a dynamic-interactional model with disorder-specific coping-oriented perspectives to improve patients’ social, emotional, and problem-solving competencies as well as stress system functional status. The enrolment of 440 patients, randomly allocated to either an intervention (*n* = 220) or control group (*n* = 220), is planned. To evaluate the intervention effect, various indicators of RA disease activity, stress system activity, and psychological condition will be assessed through sets of standardized questionnaires and biochemical analyses of blood and saliva samples. Moreover, healthcare-related costs for each patient will be obtained using routine health insurance data. Outcome variables will be measured in all patients at regular intervals prior to intervention (baseline), during the 9-month intervention (five time points), and during a 9-month follow-up phase (three time points), allowing the comprehensive analysis of within- and between-subject effects, i.e. trajectories of the target variables in the intervention and control groups. In addition, to investigate the intervention effects on real-life stress system functioning in RA, 10 integrative single-case studies (*n* = 5 from the intervention group, *n* = 5 from the control group) will be conducted. In each study, once before and after the 9-month intervention, urine samples will be collected, and patients will fill out questionnaires for approximately 1 month at 12-h intervals. Moreover, weekly in-depth interviews will be conducted with patients to determine their previous week’s emotionally positive and negative incidents. Using time series analysis, it is then possible to investigate whether and how stress system function in these RA patients has improved from the applied intervention. By using both an investigational macro- and microperspective, this project aims to evaluate a psychological intervention in the routine care of individuals with RA.

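### Read naturally, the central group-by-time test compares raw change from t0, which uses each outcome's own baseline inefficiently; the listed baseline-severity covariate does not recover the loss

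*Protocol article*

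**What the plan says.** In the protocol article, Statistical analyses, the central question is "the interaction of the intersubject factor group membership (intervention or control group) and the intrasubject factor time of measurement", explained as "the question of the target variables’ different trajectories in the intervention and control group". The model class is mixed regression: "For longitudinal data analysis, generalized linear mixed models will be estimated". The arms enter through an indicator: "Comparisons between the intervention and control groups will be directly integrated into the mixed regression models with a dichotomous indicator variable". On adjustment, one list of examples serves all outcomes: "covariates will be included in the analyses as potential predictors (e.g. age, personality, gender, the severity of illness at baseline". It does not name each outcome's own t0 value or any covariate-by-time term.

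Outcome measures counts baseline among the measurement times: "The first measurement time will be a maximum of 2 weeks prior to the intervention as a baseline". The Abstract does the same: "Outcome variables will be measured in all patients at regular intervals prior to intervention (baseline), during the 9-month intervention (five time points", followed by three follow-up points, and it ties the whole series to the trajectories compared between arms. The article does not say outright whether t0 is a response or a covariate.

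**The concern.** If t0 is one of nine levels of the time factor and the group term is free, the group-by-visit contrast at any later visit is the between-arm difference in change from t0. In a randomised comparison that is a valid estimate, but it is less precise than one that conditions on the t0 value whenever rho is below 1.

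The covariate list can hide this. A reader who sees baseline illness severity there may take it that baseline is dealt with. A covariate that is constant within a patient and enters only as a main effect shifts all of that patient's visits equally, so it drops out of a within-patient contrast. This is so even when the covariate is the outcome's own baseline.

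At stake is precision already paid for: the questionnaires, disease-activity scores, pain rating and immunoendocrine markers are all measured at t0. Recruitment has closed with 73 patients, so precision can no longer be bought with numbers.

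**Working it through.** **Inputs from the article.** Nine visits, t0 to t8 (Outcome measures). Effect f = 0.1, which is d = 0.2 for two equal groups; power above 0.8; 220 per arm; 20% dropout, so 0.8 × 220 = 176 per arm (Population, recruitment, and allocation). Enrolled: 34 control and 39 intervention, with 10 withdrawals, so 63 remain (Trial status). Alpha is 0.05, taken as two-sided.

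**Assumed.** rho, since none is given; unit SD; equal correlation across visits.

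**The plan's own figure.** Power above 0.8 comes from a simulation whose tested contrast and correlation are not given, so it cannot be reproduced. A single-visit comparison at d = 0.2 gives 55.5% power with 220 per arm and 46.7% with 176. A standard within-between interaction formula at N = 352 gives 88.5% to 99.8% with two visits (rho 0.3 to 0.7). The stated figure is attainable and is not challenged here.

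**Variance per visit.**
- Raw change: 2(1 − rho)
- Conditioned on own t0 value: 1 − rho²
- Ratio: (1 − rho²) / [2(1 − rho)] = (1 + rho)/2

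An exact generalised least squares calculation for nine visits and 176 per arm agrees. At rho 0.6 the standard error is 0.0953 unconstrained and 0.0853 with the arms set equal at t0. The closed forms are √(2/176) × √0.8 and √(2/176) × √0.64.

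**Power from an assumed 80% per visit.** Power = Φ(2.80/√ratio − 1.96).

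| rho | ratio | power after conditioning |
|---|---|---|
| 0.5 | 0.75 | 89.9% |
| 0.6 | 0.80 | 87.9% |
| 0.7 | 0.85 | 86.0% |
| 0.8 | 0.90 | 84.0% |

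**At the plan's d = 0.2 and 176 per arm**, per-visit power rises from 46.7% to 58.2% (rho 0.5), 55.5% to 65.0% (0.6), 67.8% to 74.8% (0.7) and 84.3% to 87.8% (0.8).

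**At the enrolled size.** √(1/34 + 1/39) = 0.2346. The detectable effect at 80% power is 2.80 × 0.2346 × √(variance factor).
- rho 0.5: 0.657 × √1.00 = 0.66 SD, against 0.657 × √0.75 = 0.57 SD
- rho 0.7: 0.657 × √0.60 = 0.51 SD, against 0.657 × √0.51 = 0.47 SD

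At d = 0.2, power goes from about 14% to 17% (rho 0.5) and from about 20% to 22% (rho 0.7). With the 63 remaining patients the gain is again about 2 to 3 points.

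**Does the severity covariate help?** One simulated data set per scenario, rho 0.6, random-intercept linear model. With complete data the interaction estimate was 0.2917 with standard error 0.0966 in all three fits: no covariate, severity as a main effect, own baseline as a main effect. With 20% dropout the standard errors were 0.1001, 0.0999 and 0.0996. With t0 taken out of the responses and own baseline by visit as covariate, they fell to 0.0861 (complete data) and 0.0927 (dropout).

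**The case against.** The strongest reply is that the article does not fix the model. It states a question, a model class and an open list of example covariates. A baseline-conditioned or constrained model is not excluded, and a full protocol that is not shown may specify one. This stands in part: t0 as a response is an inference, though the natural one. The other reading does not save the stated test. If only t1 to t8 were responses, a benefit that is constant from t1 onward would sit in the group main effect, and the interaction would miss it.

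Some stronger readings are tempting but not supported.
- *The outcome's own baseline is not used at all.* It is used, because change subtracts it. Raw change beats a comparison of later values alone whenever rho exceeds 0.5: at rho 0.7, d = 0.2 and 176 per arm, 67.8% against 46.7%. It is used inefficiently.
- *The trial loses 6 to 10 power points per visit.* That range needs both rho of 0.5 to 0.7 and 80% power at a single visit. The article gives neither, and its power figure is not stated to be per visit.
- *Better baseline use rescues the shortfall in recruitment.* At d = 0.2 it adds about 2 to 3 points to power that is already very low.
- *The planned test is biased.* Under randomisation it is not. A chance imbalance at t0 is handled less well by raw change, but that is the same loss of precision seen from another side.
- *The severity covariate cancels exactly in every model.* This was shown only for linear models with complete data. With dropout it nearly cancels, and models with other link functions were not checked.

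**Conclusion.** The point holds as an efficiency loss that is cheap to avoid, conditional on reading t0 as a response level with a free group term. Conditioning cuts the per-visit variance to (1 + rho)/2 of its value, 0.75 to 0.90 for rho 0.5 to 0.8. From an assumed 80% start that is worth about 10 points at rho 0.5, falling to 4 at rho 0.8. At the enrolled size the practical return is a detectable effect smaller by 0.09 SD (rho 0.5) or 0.04 SD (rho 0.7).

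The per-visit figures do not carry over to the joint interaction test. For an 8-degree-of-freedom test with a constant d = 0.2 and 176 per arm, power is 46.6% unconstrained against 69.1% constrained at rho 0.6. If the effect instead builds up to t5, it is 61.6% against 72.7%. The size there depends on the effect profile as well as on rho.

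The point covers only outcomes measured at t0. It does not reach insurance costs accumulated over the 18 months.

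**What to change.** In Statistical analyses, state for each outcome measured at t0 whether t0 is a response or a covariate, and use one of two forms:
- take the scheduled visits from t1 to t8 as responses, with that outcome's own t0 value and its interaction with visit as covariates; or
- keep t0 as a response and constrain the arms to be equal at t0, which also keeps patients with no t0 value.

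The t0 value should not be both a response and a covariate in the same model. Test the arm difference at each visit and its average over t1 to t8. Illness severity may stay as a covariate, but as a main effect it should not be counted as baseline adjustment for the interaction. Any power gain should be quoted as a range over rho.

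The cost is a change of wording and of model formula, with no new data or patients. The covariate form spends a few degrees of freedom on the t0-by-visit terms and needs a rule for missing t0 values.
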